### Interim analyses {21b}

There is no interim analysis planned for this study.

### Methods for additional analyses (e.g., subgroup analyses) {20b}

Subgroup analysis will be carried out for participants predicted to be low, high, and normo-responders.

### Methods in analysis to handle protocol non-adherence and any statistical methods to handle missing data {20c}

Non-adherence to the trial protocol would imply that the participant has not received the intervention planned. These participants will be considered as having withdrawn from the trial. This per-protocol analysis strategy ensures that our study results accurately reflect the outcomes for those participants who fully adhered to the intervention protocol.

Missing covariates would immediately be considered as exclusion criteria, as they are necessary for the randomization and/or the use of the IDoser.

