### Trial design {8}

The trial design is a single-blinded RCT with two arms with a 1:1 allocation ratio, comparing outcomes following FSH dose selection by IDoser and dosing based on standard clinical practice.

The hypothesis that will be tested is whether the performance of IDoser selecting the first dose of FSH is non-inferior to the standard clinical protocol in regards to the average number of mature oocytes recovered per group. The difference in the number of MII that is regarded to be clinically significant is 2 MII. Our decision to consider a difference of two MII oocytes as clinically significant is based on empirical evidence and clinical relevance. As only 30 to 40% of inseminated mature oocytes develop into blastocysts [13, 14], the choice of two MIIs strikes a balance between statistical significance and clinical practicality, while taking into account the consequent impact on the success of fertility treatments. If the average number of MII in the intervention group is inferior in 2 or more units, IDoser will be considered inferior to the standard clinical practice.

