### Criteria for discontinuing or modifying allocated interventions {11b}

Participants can withdraw from the study at any time and for any reason or no reason. The reason for withdrawal will be recorded if patients choose to disclose this information. Failure to administer the allocated FSH dose and discontinuation of IVF/ICSI for medical reasons will also result in withdrawal. Participants will be informed immediately regarding their withdrawal from the trial, if either an error in dose administration is detected or for a medical reason. If an error in FSH administration or medical reason is detected, the participant’s treatment will be interrupted or allowed to continue based on the clinical judgment of the healthcare provider. The data of withdrawn patients obtained during their participation in the study will be included in the study analysis. Withdrawn patients will not be replaced.

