### Sample size {14}

A sample size calculation was performed to establish the number of participants required for the study. To determine a statistically significant difference equal or greater to 2 MII oocytes, 118 subjects are necessary in each group (*n *= 236), accepting an alpha risk of 0.05 and a beta risk of 0.2 in a one-sided test. We estimate a mean common standard deviation of 5.84 (as per the observational data included during development and validation of IDoser) and anticipate a drop-out rate of 10%.

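### Sections {11b} and {20c} conflict on whether women who missed the allocated FSH dose are analysed, and the only strategy named for the non-inferiority test is per-protocol

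*Protocol article*

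**What the plan says.** Section {11b} of the protocol article lists what leads to withdrawal: "Failure to administer the allocated FSH dose and discontinuation of IVF/ICSI for medical reasons will also result in withdrawal". It leaves to the treating clinician whether treatment goes on after a dosing error, and then says: "The data of withdrawn patients obtained during their participation in the study will be included in the study analysis".

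Section {20c} defines non-adherence as not having received the planned intervention and treats such women as withdrawn. It describes the approach thus: "This per-protocol analysis strategy ensures that our study results accurately reflect the outcomes for those participants who fully adhered to the intervention protocol".

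No other analysis strategy is named for the primary comparison. The margin comes from section {8}: "The difference in the number of MII that is regarded to be clinically significant is 2 MII". Section {17a} blinds the medical team except those caring for the participant, so the treating clinician knows the arm. Section {12} records stimulation stopped before pick-up (OPU) as an outcome in its own right and gives such a cycle no MII value.

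**The concern.** Withdrawal is the shared label, and it leads to opposite handling. A woman who missed the allocated dose is in the analysis under {11b} and outside it under {20c}. Two analysts working from this text could test different women, and the choice could be made after the results are known.

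If {20c} prevails, the primary test excludes on events after randomisation. Randomisation then no longer protects the comparison when the excluded women differ between arms in number and in expected yield. Two features of this trial make that possible. The treating clinician is unblinded, and stopping treatment for medical reasons after the first dose may be a consequence of that dose. In a non-inferiority trial, losing low-yield women mainly from the IDoser arm would make IDoser look better than it is.

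**Working it through.** **The texts side by side**

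- Woman not given the allocated dose: withdrawn under both sections; data included under {11b}; not a full adherer, so left out under {20c}.
- Woman given the allocated dose, then stopped for medical reasons: withdrawn under {11b}, data included. {20c} defines non-adherence only by receipt of the planned intervention, so whether she stays in the per-protocol set is unclear.
- Cycle stopped before OPU: no MII value is assigned anywhere, so neither rule says how she enters the primary comparison.

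**Inputs from the document**

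Margin 2 MII ({8}). From {14}: "accepting an alpha risk of 0.05 and a beta risk of 0.2 in a one-sided test"; SD 5.84; drop-out 10%; 118 per arm.

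**The plan's own figure**

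n = 2 × (1.645 + 0.842)² × 5.84² / 2² = 105.4, rounded up to 106 per arm. 106 / 0.9 = 117.8, rounded up to 118. The stated size reproduces, so the sample size is not at fault.

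**Illustration 1: outcome-related exclusion in the IDoser arm only**

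Assumptions, not in the document: 10% of IDoser women are excluded and average 3 to 5 fewer MII than those kept; control losses are unrelated to yield; 106 per arm remain; the true difference among all randomised is −2.

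- Overstatement of the IDoser mean = 0.10 × 3 = 0.3 to 0.10 × 5 = 0.5 MII, or 15 to 25% of the margin.
- SE = 5.84 × √(2/106) = 0.802.
- False non-inferiority = Φ(bias/SE − 1.645): Φ(0.3/0.802 − 1.645) = 0.10; Φ(0.5/0.802 − 1.645) = 0.15. With no bias it is 0.05.
- If control loses nobody (118 against 106), SE = 5.84 × √(1/118 + 1/106) = 0.782, and the results are 0.10 and 0.16.

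**Illustration 2: excluded women have zero MII**

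Assumptions: control adherers average 8 or 10 MII; SD 5.84; true all-randomised difference −2. Example with 5% of control and 10% of IDoser excluded and a control mean of 8: the control all-randomised mean is 0.95 × 8 = 7.6, IDoser is 5.6, IDoser adherers average 5.6/0.90 = 6.22, and the per-protocol difference is 6.22 − 8 = −1.78.

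| Excluded, control / IDoser | Per-protocol difference (control mean 8 / 10) | False non-inferiority |
|---|---|---|
| 5% / 10% | −1.78 / −1.67 | 8.6% / 11.1% |
| 5% / 15% | −1.41 / −1.18 | 18.1% / 26.8% |
| 10% / 20% | −1.50 / −1.25 | 14.9% / 23.1% |
| 10% / 10% | −2.22 / −2.22 | 2.7% / 2.7% |

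The last row shows that equal, similar exclusion does not inflate the error.

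**The opposite risk: dilution in an all-randomised analysis**

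If a share q of IDoser women in effect receive control-type dosing, a true −2 becomes −2(1 − q). With 118 per arm, SE = 5.84 × √(2/118) = 0.760. For q = 5%, 10% and 20% the difference is −1.9, −1.8 and −1.6, and false non-inferiority is 6.5%, 8.3% and 13.2%.

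**Power at a true difference of 0**

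118 per arm: Φ(2/0.760 − 1.645) = 83.8%. 106 per arm: Φ(2/0.802 − 1.645) = 80.2%.

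**The case against.** The two sections can be brought closer than they first appear. {11b} keeps only data gathered during participation, and a woman is told at once that she is withdrawn when a dosing error is found. MII are counted later, at OPU. If the error is found on the first day of stimulation, her MII count could be said to arise after participation ended, leaving {20c} to govern the primary comparison. A reader might therefore infer a flat contradiction for every withdrawn woman, and the text does not support that. What stands is narrower but enough: errors found at or after OPU and medical discontinuations remain contested, the study analysis that {11b} refers to is not defined, and the text does not say whether a mis-dosed woman who goes on to OPU still counts as participating.

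A reader might also infer that clinicians will override IDoser doses and that their exclusion will favour IDoser. The document describes no override. It names administration errors and medical reasons, which can occur in either arm, and a study nurse verifies the dose. No rate or direction of deviation is given. An overridden woman would also show the yield of a clinician-chosen dose, so an all-randomised analysis would not undo that bias and would itself be diluted. This part of the objection stands, and it is why the fix asks for both analyses.

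Finally, an analysis of all randomised women may appear in a full protocol or SAP that is not shown. Its absence here is not the point; the point is two statements that do not fit together and the one strategy that is named.

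**Conclusion.** The conflict between {11b} and {20c} is real on the text and needs no calculation. It leaves the analysis set of the primary non-inferiority test open and points towards a per-protocol-only test.

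The bias is a possibility, not a demonstrated effect. It needs exclusions that differ by arm and relate to outcome. The figure of about 10 to 15% false non-inferiority rests on 10% outcome-related exclusion in the IDoser arm with no counterpart in control. The 9 to 27% range in the table rests on zero yield in excluded women and 5 to 10 points more exclusion in the IDoser arm. The plan's 10% is overall drop-out and should not be read as a forecast of either.

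A reader might infer that analysing all 118 per arm removes the problem and lifts power to 84%. Neither is secured. Dilution can also favour non-inferiority, and the 84% holds only if every woman has an MII value and the SD stays at 5.84 once stopped cycles are counted.

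**What to change.** Reconcile {11b} and {20c} so that both give the same rule, and then:

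- Define an all-randomised set, analysed by allocated arm, in which women with dosing errors stay in and their outcomes are collected.
- Define a per-protocol set with its exclusions listed, saying explicitly whether medical discontinuation after the first dose is one of them.
- State how a cycle stopped before OPU counts for MII (for example as zero, with a sensitivity analysis), and how women who withdraw consent without an MII count are handled.
- Claim non-inferiority only if both analyses meet the 2 MII margin.

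This concerns analysis and data handling only; the clinician's decision on continuing treatment is untouched. The cost is protocol and SAP wording, since outcomes already come from routine records. Requiring both analyses to agree is slightly stricter than relying on one, and the SD of 5.84 should be checked against the rule chosen for stopped cycles.

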### Plans to give access to the full protocol, participant-level data, and statistical code {31c}

Fully anonymized participant level data and the statistical code used for this trial will be made available by the corresponding author on reasonable request.

## Oversight and monitoring

### Composition of the coordinating center and trial steering committee {5d}

This is a multicenter trial, where the coordinating center is Clinica Eugin in Barcelona. Daily support for the study is provided by the:Principal investigator: supervises the trial and coordinates the study teamData coordinator: manages data annotation and data safety and qualityResearch team: includes both principal investigator and data coordinator, together with co-investigators in charge of data outcome analysisMedical team: in charge of participant recruitment, handling of informed consent forms, follow-up of participants, and safety monitoring according to protocolThere is no steering committee.

### Composition of the data monitoring committee, its role and reporting structure {21a}

The unblinded data coordinator will be in charge of monitoring safety and quality of data and will report to the principal investigator. The data coordinator is not independent from the sponsor. The research team has no commercial conflict of interest.

### Adverse event reporting and harms {22}

Clinical study participants will be routinely asked about adverse events (quantity and quality) at each study visit. Any adverse event that may occur to the participants of the study must be documented and followed up by the investigator. The event will be documented with the necessary investigations for adequate assessment of causality as established in the document “MDCG 2020-10/1- Safety reporting in clinical investigations of medical devices under the Regulation (EU) 2017/745.” Serious adverse events must be immediately notified to the sponsor, who will be in charge of reporting the events to the ethics committee and the competent authorities. The sponsor must report serious adverse events within 15 days (7 days in case of death or a life-threatening event) using the official serious adverse events notification forms. The sponsor will report the serious adverse events through Eudavigilance-CT.

### Frequency and plans for auditing trial conduct{23}

This trial is subject to external audit independent from investigators and the sponsor, annually. The data coordinator will perform internal audits quarterly, by randomly selecting a subset of participants and crosschecking the electronic data table and informed consents.

### Plans for communicating important protocol amendments to relevant parties (e.g., trial participants, ethical committees) {25}

Any amendment to the trial protocol will be reported to the ethics committee and competent authorities and only applied after their approval.

### Dissemination plans {31a}

Plans to disseminate results and conclusions of the trial include scientific papers and/or congress communications.

## Discussion

The current literature includes several FSH dosing models [5, 6, 8, 10] that when tested prospectively [7, 9, 10] show improvement in outcomes. This includes a reduction in OHSS risk and a higher proportion of patients within the optimal range. Nonetheless, none of these models consider patients over the age of 40 years or non-normo-ovulatory women in their development nor in the respective RCTs. As such, the applicability of current models remains limited. The trial presented would evaluate an all-inclusive, comprehensive FSH model for COS, named IDoser. This kind of trial for interventional ML models is sparse in literature, but necessary for a safe clinical application of any medical device of this nature.

## Trial status

Registered in ClinicalTrials.gov, under identifier NCT05948293, on 14 July 2023. Recruitment has not started yet; it is estimated to start in October 2023 and end October 2024. Current protocol version is version 2 from 2 February 2023.

## Data Availability

Anonymized data will be shared upon reasonable request.

## Abbreviations

IVF: In vitro fertilization
ICSI: Intracytoplasmic sperm injection
MII: Metaphase II
COS: Controlled ovarian stimulation
FSH: Follicle-stimulating hormone
OPU: Oocyte pick-up
OHSS: Ovarian hyperstimulation syndrome
BMI: Body mass index
AMH: Anti-Müllerian hormone
AFC: Antral follicle count
RCT: Randomized controlled trial
LH: Luteinizing hormone
IU: International units
COCs: Cumulus-oocyte complexes
GDPR: General data protection regulation
SD: Standard deviation
